## Abstract

**Background:**

Smartphones have become integral to people’s lives, with a noticeable increase in the average screen time, both on a global scale and, notably, in India. Existing research links mobile consumption to sleep problems, poor physical and mental health, and lower subjective well-being. The comparative effectiveness of monetary incentives given for self-selected versus assigned targets on reducing screen time and thereby improving mental health remains unanswered.

**Objective:**

This study aims to assess the impact of monetary incentives and target selection on mobile screen time reduction and mental health.

**Methods:**

We designed a 3-armed randomized controlled trial conducted with employees and students at an educational institution in India. The study is conducted digitally over 12 weeks, including baseline (2 weeks), randomization (1 week), intervention (5 weeks), and postintervention (4 week) periods. We emailed the employees and students to inquire about their interest in participation. Those who expressed interest received detailed study information and consent forms. After securing consent, participants were asked to complete the initial survey and provide their mobile screen time during the baseline period. At the beginning of the intervention period, the participants were randomly allocated into 1 of 3 study groups in a 2:2:1 ratio (self-selected vs assigned vs control). Participants in the self-selected group were presented with 3 target options: 10%, 20%, and 30%, and they were asked to self-select a target to reduce their mobile screen time from their baseline average mobile screen time. Participants in the assigned group were given a target to reduce their mobile screen time from their baseline average mobile screen time. The assigned target was set as the average of the targets selected by participants in the self-selected group. During the intervention period, participants in the self-selected and assigned group were eligible to receive a monetary incentive of INR (Indian Rupee) 50 (US $0.61) per day for successfully attaining their target. Participants in the control group neither received nor selected a target for reducing their mobile screen time and did not receive any monetary incentives during the intervention period. All participants received information regarding the advantages of reducing mobile screen time. As an incentive, all participants would receive INR 500 (US $6.06) upon completion of the study and a chance to win 1 of 2 lotteries valued at INR 5000 (US $60.55) for consistently sharing their mobile screen time data.

**Results:**

Currently, the study intervention is being rolled out. Enrollment occurred between August 21, 2023, and September 2, 2023; data collection concluded in November 2023. We expect that results will be available by early 2024.

**Conclusions:**

The monetary incentives and self-selected versus assigned targets might be effective interventions in reducing mobile screen time among working professionals and students.

**Trial Registration:**

AsPredicted 142497; https://aspredicted.org/hr3nn.pdf

**International Registered Report Identifier (IRRID):**

DERR1-10.2196/53756

## Introduction

Smartphones have become ubiquitous in people’s lives. The global average for daily screen time is 6 hours and 37 minutes [1]. In 2021, India had a mobile subscriber count of 1.2 billion, and around 750 million of them were using smartphones [2]. The average screen time for Indians has increased to 7.3 hours [3]. As of 2019, the leading mental disorders are depression and anxiety, which affect 280 million and 301 million people worldwide, respectively [4]. Estimates suggest that over 197 million Indians, approximately 15% of our population, experience mental disorders. Of these, approximately 85 million experience depression- and anxiety-related disorders [5]. Existing research links excessive screen time to lower subjective well-being, depression, anxiety, sleep disorders, and poor physical health [6-13].

Numerous correlational studies have explored the relationship between digital media use and well-being, with many of them indicating that screen time and mobile consumption are negatively linked to subjective well-being [6-10,14]. For instance, Przybylski and Weinstein [15] explored the effect of digital media use on the well-being of adolescents, providing support for the Goldilocks hypothesis—individuals with moderate use have higher well-being than those with lower and higher use.

On the other hand, Twenge and Campbell [14] showed that although light users of digital media had higher well-being than people who abstain, moderate and heavy users had lower well-being than light users. Twenge and Martin [7] demonstrated that the associations between greater digital media use and psychological well-being are greater for female than male individuals. In their correlational study, Twenge and Campbell [14] found that individuals with moderate and heavy digital media use (smartphones, social media, and others) had lower well-being than those with lighter media use, especially individuals with greater than 5 hours of digital media use per day. Orben and Przybylski [16] used specification curve analysis to understand if there is any correlational relationship between digital media use and well-being among adolescents. They found a negative but small association, explaining at most 0.4% of the variation in well-being [16].

In addition, existing research has also shown that temporary monetary incentives and targets can be used to inculcate behavioral change in domains such as gym attendance [17], smoking, work behavior [18], alcohol abuse [19], and weight loss [20]. Research studies suggest that temporary monetary incentives and specific targets can effectively reduce social media use and allow people to limit their screen time [21].

However, the current body of research does not provide evidence regarding whether self-selected targets or externally imposed targets are more effective in promoting and maintaining behavioral change, especially in the context of smartphone use, thereby improving mental health. Reducing smartphone screen time is essential for maintaining a healthy and productive lifestyle.

In this study, we aim to nudge people to reduce their screen time by providing temporary monetary incentives and targets. Target is defined as the minimum percentage reduction in daily mobile screen time from the daily average mobile screen time during the baseline period.

The objectives of the study are as follows:

To estimate the impact of monetary incentives and targets on reducing mobile screen time during the treatment and posttreatment period.To evaluate the efficacy of self-selected versus assigned targets in reducing mobile screen time.To estimate the impact of screen time reduction on mental health. Mental health will be assessed using measures such as Generalized Anxiety Disorder–7 (GAD-7) for anxiety, Patient Health Questionnaire–9 (PHQ-9) for depression, daily mood survey for mood, and well-being scores for general well-being.

## Methods

### Study Design and Setting

To achieve the study objectives, we are conducting a pragmatic, 3-arm, parallel-group, randomized controlled trial involving students and employees of the Indian School of Business (ISB). The ISB operates across 2 campuses located in the states of Punjab and Telangana, India. The randomized controlled trial spans a 12-week duration, comprising 2 weeks of baseline, 1 week for randomization, 5 weeks of intervention, and 4 weeks of the postintervention period.

### Participants and Eligibility Criteria

Current employees and students at both ISB campuses who had Android-operated mobile phones and were available throughout the 12-week study period were eligible to participate in the study. The study excluded employees affiliated with the implementing department, Max Institute of Healthcare Management, ISB, as they previously participated in the study’s pilot.

### Recruitment

The study was conducted entirely through digital communication, avoiding the need for in-person interaction between the researchers and the participants. We initiated the study by sending an email through the Head of Student Affairs and Human Resources to both employees and students of ISB to their official email addresses. The email included a link to a form that allowed participants to express their interest in the study. This email was sent 3 times. Recruitment took place for 2 weeks, the preregistration period, to gather expressions of interest. Potential participants who expressed interest were subsequently provided with study details and consent forms. Three email reminders were sent to the potential participants to provide consent. The participants who provided consent were asked to complete the baseline survey and provide their mobile screen time data during the baseline period.

### Randomization and Blinding

After obtaining the baseline mobile screen time data, participants were randomly assigned to 1 of 3 groups in a 1:2:2 (control vs self-selected vs assigned) ratio. This assignment was carried out using a stratified randomized permuted block design with a block size of 5 using the *ralloc* command on Stata 17 software (StataCrop LLC). The allocation was stratified based on 2 variables: status in the institute (employee or student) and the quartile of baseline average mobile screen time. Following randomization, the research team became aware of the allocation groups. Blinding at the participant level was not possible due to the nature of the intervention. Participants were informed about their group before the start of the intervention period. They were not told about other groups or the groups of other participants. The CONSORT (Consolidated Standards of Reporting Trials) flow diagram for the study is provided in Figure 1.

**Figure 1 figure1:**
[figure not shown]
The CONSORT (Consolidated Standards of Reporting Trials) flow diagram for the study.

### Sample Size

The target sample was 300 participants, assuming a conservative effect size (*d*) of 0.12 for the difference between self-selected and assigned conditions and 0.15 for the difference between the intervention group and control conditions, with 80% power and an α of .05. The effect size was estimated based on past studies in this domain [22,23].

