### Statistical Analysis

We will estimate the effects of mobile screen time, target achievement rate, GAD-7, PHQ-9, and daily mood scores by comparing variables of interest between the intervention and baseline and between the postintervention and baseline periods. To perform this analysis, we will use Stata 17 and R (version 4.2.2; Free Open-Source Software). The unadjusted effects will be calculated as differences in the means and conducting a 2-tailed Student *t* test for significance. For adjusted effects, we will use simple ordinary least square regression adjusting for participant-level covariates: age, gender, and employee or student. We assume errors to be correlated within each participant but uncorrelated across participants. A separate equation will be used for each dependent variable. The regression equations are provided in Multimedia Appendix 1. For mobile screen time, we will estimate a difference-in-difference ordinary least square regression. To account for the impact of the intervention and the postintervention period, we will incorporate dummy variables for the period. Specifically, assessing the effect on mobile screen time and target achievement rate postintervention will provide valuable insights into habit formation. Multilevel or hierarchical linear modeling will also be used to allow differential relationships between mood and screen time at the individual level.

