## Results

We started the recruitment process on August 21, 2023. We randomized 156 participants, and at the original submission of the protocol, we completed 3 weeks of the intervention period. The results are expected to be published in early 2024. The study results will be published in academic journals. These published findings have the potential to guide policy makers in establishing guidelines for monitoring and limiting excessive mobile screen exposure among both working professionals and students.

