### Limitations

One of the potential limitations of the study is that the analyses in the study may lack sufficient power to detect the anticipated effects due to low enrollment. Another limitation is requesting the weekly submission of screen time through a mobile app, which might increase overall mobile screen time. However, this task only demands 4-5 minutes of weekly effort and will not impact the results, as the same procedure was also used at the baseline. The daily mood score was collected through a messaging app, WhatsApp, which is another limitation of the study.

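### The stated 80% power at d = 0.12 and d = 0.15 with 300 participants cannot be reproduced from the stated inputs: a two-group comparison gives about 15% and 18%

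*Protocol article*

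**What the plan says.** All references are to the protocol article.

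- **Methods, Sample Size:** "The target sample was 300 participants". For the two intervention arms against each other the assumed d is 0.12. For the other contrast the section assumes "0.15 for the difference between the intervention group and control conditions, with 80% power and an α of .05". Both values are described as conservative and are taken from two cited studies. The section gives no SD unit for d, no number of measurements, no correlation and no named test.
- **Methods, Randomization and Blinding:** allocation is in a "1:2:2 (control vs self-selected vs assigned) ratio".
- **Methods, Statistical Analysis:** unadjusted effects are "differences in the means and conducting a 2-tailed Student" t test. Screen time is also to be analysed by a difference-in-difference regression with errors correlated within participant. The equations are in an appendix that is not shown.
- **Results:** "We randomized 156 participants".
- **Discussion, Limitations:** the analyses "may lack sufficient power to detect the anticipated effects due to low enrollment".

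**The concern.** Standardized differences of 0.12 and 0.15 are very small, and two-group comparisons of that size usually need thousands of participants for 80% power. A target of 300 split over three arms is far below that. The article prints effect size, power, significance level and sample size together, so the reader can check one against the others, and on the ordinary meaning of d they do not fit.

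Self-selected versus assigned targets is the trial's novel question. If that comparison is not significant, the Sample Size and Limitations sections together invite the reading that an adequately powered design merely under-recruited. On the stated inputs, full recruitment would not have supplied the stated power either.

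**Working it through.** **Inputs.** N = 300; d = 0.12 and 0.15; power 80%; α = 0.05 (Sample Size). Ratio 1:2:2 (Randomization and Blinding), so 60 control, 120 self-selected and 120 assigned. Two-sided t test (Statistical Analysis). 156 randomized (Results), taken as 62 v 62 for the two intervention arms and 125 v 31 for intervention versus control.

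**1. Attempt to reproduce the 80%.** Noncentral t with noncentrality d / √(1/n1 + 1/n2):

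| Contrast | Groups | Noncentrality | Two-sided power | One-sided power |
|---|---|---|---|---|
| d = 0.12 | 120 v 120 | 0.12 / 0.1291 = 0.93 | 15% | 24% |
| d = 0.15 | 240 v 60 | 0.15 / 0.1443 = 1.04 | 18% | 27% |

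At 156 the two-sided figures are about 10% and 12%.

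**2. Sample size for 80%.** (1.960 + 0.842)² = 7.849.
- d = 0.12: per arm 2 × 7.849 / 0.0144 = 1,090. At 1:2:2 the total is 2.5 × 1,090 = 2,725.
- d = 0.15: controls (1 + 1/4) × 7.849 / 0.0225 = 436. The total is 5 × 436 = 2,180.

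**3. Other readings of the effect size.**
- As Cohen's f, 0.12 with equal groups means d = 2f = 0.24, and power is 46%. With a 240:60 split, f = d√(0.8 × 0.2) = 0.4d, so 0.15 means d = 0.375, and power is about 74%. Both fall short.
- As f², power exceeds 99%, which does not lead to a target of 300 either.
- Two arms of 150 give 18% and 25%. Arms of 300 each give 31% and 45%.

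**4. What a longitudinal calculation would need.** To reach 80% at 300, the error variance must fall to [d / (2.802 × √(1/n1 + 1/n2))]² of the SD² behind d. That is 0.110 for d = 0.12 and 0.138 for d = 0.15. None of the correlations or variance shares below is in the article; they are assumptions that show the range.

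- *Between-person SD, baseline-adjusted:* 1 − ρ² must equal 0.110 or 0.138, so ρ must be about 0.94 or 0.93.
- *Weekly SD, 2 baseline and 5 intervention weeks, compound symmetry:* the variance factor is (1 − ρ)(1/2 + 1/5).
- *Single-day SD, 14 and 35 days, ICC 0.5, person-by-period variance share p in each period:* the factor is 2p + (0.5 − p)(1/14 + 1/35).

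| Unit of d | Assumption | Factor | Power, d = 0.12 | Power, d = 0.15 |
|---|---|---|---|---|
| Weekly | ρ = 0.5 | 0.350 | 35% | 42% |
| Weekly | ρ = 0.85 | 0.105 | 82% | 89% |
| Single day | p = 3% | 0.107 | 81% | 89% |
| Single day | p = 10% | 0.240 | 48% | 56% |

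**5. Effects detectable with 80% power, two-group comparison (noncentral t).**
- At 300: d = 0.36 (120 v 120) and 0.41 (240 v 60).
- At 156: d = 0.51 (62 v 62) and 0.57 (125 v 31).
- At 156 with baseline adjustment and an assumed ρ of 0.7, multiply by √(1 − 0.49) = 0.714: about 0.36 and 0.40.

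**The case against.** The Sample Size section names neither a test nor an SD unit. Screen time is recorded daily, and its planned regression is a difference-in-difference on repeated data. The equations are in an appendix and the effect sizes come from cited studies, neither of which is shown, and an article may leave such detail to the full protocol. A longitudinal calculation could well lie behind the 80%, and several plausible sets of inputs reach it: weekly SD units with ρ = 0.85, single-day units with 3% person-by-period variance, or a repeated-measures ANOVA on f with ρ = 0.5. The Limitations section also admits that power may be lacking.

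Much of this stands. A reader might infer from the 15% and 18% that the design is shown not to have 80% power, or that it could see only effects about three times those assumed. The document does not support either as an unconditional statement, because both hold only if d is in between-person SD units and the comparison is cross-sectional.

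What does not stand is that this rescues the printed claim. The article calls the effect d and states none of the longitudinal inputs. Over the assumptions tabulated above, power for d = 0.12 runs from 35% to 82%. The admission in the Limitations section names low enrollment only.

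Two further inferences should also be left aside. The Sample Size section ties no power claim to the GAD-7 or PHQ-9, so their being measured once per stage does not bear on the stated figure. And nothing in the article proposes to read a non-significant difference as equivalence.

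**Conclusion.** The concern holds in this form: 80% power at 300 is not reproducible from the stated inputs. Under the stated allocation and two-sided t test it is about 15% for d = 0.12 and 18% for d = 0.15, and the required totals are about nine (2,725 / 300) and seven (2,180 / 300) times the target. A one-sided test or reading the values as Cohen's f does not close the gap.

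These figures rest on d being in between-person SD units and on a comparison without repeated measures. With other, unstated inputs 80% is attainable, so the document supports a finding of an unsupported figure, not proof that the design lacks that power. On the stated inputs, low enrollment is not the whole explanation that the Limitations section makes it.

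**What to change.** 1. In Sample Size, state the SD unit of d, the number of measurements per period and the correlations (or variance components) that give 80% power at 300 for each contrast.
2. If no such calculation exists, replace the 80% statement with the detectable effects for a two-group comparison: d of about 0.36 (self-selected versus assigned) and 0.41 (intervention versus control) at 300, and about 0.51 and 0.57 at the 156 randomized. The baseline-adjusted figures of about 0.36 and 0.40 at 156 may be added, with ρ = 0.7 declared as an assumption.
3. If the figure is corrected, amend Limitations to say that the planned 300 was also too small for the assumed effects, and report the self-selected versus assigned difference with its confidence interval.

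The cost is wording only. No participants, procedures or analyses are added. If step 2 applies, the stated figure becomes less favourable.

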### Interventions

At the end of the baseline period, the participants were randomized into 3 groups: the control group and 2 intervention groups.

#### Intervention-1 (Self-Selected Group)

In this group, participants were asked to select a target to reduce their mobile screen time from their baseline average mobile screen time. They were presented with 3 target options (10%, 20%, and 30%) and were asked to select one of the targets. The target options were chosen such that none of the targets is unreasonably high, ensuring that there are at least some participants who chose the target. Additionally, we want to ensure that the targets are sufficiently different so that participants are not indifferent between them. During the intervention period, participants in this group were eligible to receive a monetary incentive of INR (Indian Rupee) 50 (US $0.61) per day for successfully achieving the target they selected.

#### Intervention-2 (Assigned Group)

In this group, participants were assigned a target to reduce their mobile screen time from their baseline average. This target was determined after the participants in the self-selected group chose their respective targets. The assigned target was determined as the average of the targets selected by participants in the self-selected group. This was done such that both groups have the same average screen time reduction target, and thereby we can compare the average screen time reduction between the groups. This makes the intervention arms on average only differ in whether they chose or were assigned a screen time reduction target. During the intervention period, participants in this group were eligible to receive a monetary incentive of INR 50 (US $0.61) per day for successfully achieving the assigned target.

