In this study, we expect the screentime reduction target to vary at the individual level. There might be cases when the average target is higher than the individual reduction that some individuals will prefer to achieve, while for some others there might be cases when the target is less than the individual reduction they will aim to achieve. In the former case, the participants may not be able to achieve the average target, while in the latter case, they will achieve it. Other psychological factors, such as cognitive dissonance, support the idea that the self-selected condition is likely to outperform the assigned target condition. This is because participants are motivated to follow through on their personally chosen targets. So overall the reduction in exogenous (assigned group) condition could be lower due to this reason as well.

Through rigorous research design and a comprehensive examination of various factors, the results from the study make a substantial contribution to enhancing the comprehension of how self-selected versus assigned targets may potentially reduce mobile screen use and thereby improve mental health.

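### Matching the assigned target to the mean of the chosen targets does not make choice versus assignment the only difference between the two incentive arms; the contrast is a package comparison

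*Protocol article*

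**What the plan says.** In the Protocol article, under Intervention-1 (Self-Selected Group), the menu is fixed: "They were presented with 3 target options (10%, 20%, and 30%) and were asked to select one of the targets". The options were set with the aim of "ensuring that there are at least some participants who chose the target", so targets are meant to spread over the menu.

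Under Intervention-2 (Assigned Group), "The assigned target was determined as the average of the targets selected by participants in the self-selected group". The stated purpose is an equal mean: "This was done such that both groups have the same average screen time reduction target". The inference follows directly: "This makes the intervention arms on average only differ in whether they chose or were assigned a screen time reduction target".

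Both arms are paid INR 50 for each day on which the participant's own target is met, and nothing for a day on which it is missed. Statistical Analysis lists target achievement rate among the outcomes.

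Under Principal Findings in the Discussion, the authors write: "In this study, we expect the screentime reduction target to vary at the individual level". They go on: "There might be cases when the average target is higher than the individual reduction that some individuals will prefer to achieve", with the opposite case for others, and say that this affects who meets the target. A further mechanism is then added: "Other psychological factors, such as cognitive dissonance, support the idea that the self-selected condition is likely to outperform the assigned target condition".

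**The concern.** Equal means are one property of two distributions. The sentence under Intervention-2 moves from that property to a claim that only the act of choosing separates the arms. Two other differences remain:

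- **Spread.** One arm has several target values; the other has a single value.
- **Fit.** In one arm the target is picked by the person who has to meet it; in the other it takes no account of the person.

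The Discussion treats poor fit of the common target as one reason for a difference and the psychological effect of choosing as another. Two reasons cannot both operate if the arms differ in one respect only.

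The all-or-nothing daily payment matters here. The response to a threshold need not be linear in the threshold, so equal average targets need not produce equal average effort. The achievement rate depends on the target distribution by definition. What is at stake is the conclusion of the second objective: whether a difference between these arms may be reported as the effect of choosing.

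**Working it through.** **Inputs.** From the document: the 10/20/30% menu, the common-mean rule, the all-or-nothing daily payment, target achievement rate as an outcome, and the planned d = 0.12 for self-selected versus assigned (Sample Size). The document does not give the choice shares, the distribution of reductions or baseline minutes, so those below are assumptions shown as ranges. There is no stated figure for this point to reproduce; d = 0.12 serves only as a yardstick.

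**Step 1: spread of the targets.** With choice shares w on targets t and mean m = Σwt, SD = √Σw(t − m)².

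| Shares at 10/20/30% | Mean (assigned target) | SD, self-selected | SD, assigned |
|---|---|---|---|
| 1/3, 1/3, 1/3 | 20 | 8.2 | 0 |
| 20, 60, 20 | 20 | 6.3 | 0 |
| 50, 30, 20 | 17 | 7.8 | 0 |
| 50, 0, 50 | 20 | 10.0 | 0 |

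Example, third row: √(0.5×49 + 0.3×9 + 0.2×169) = √61 = 7.8. With 80% on the middle option and 10% on each side the SD is 4.5. It reaches 0 only if everyone picks the same option.

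**Step 2: achievement rate from spread alone.** Let the daily reduction be N(μ, σ) and ignore the target altogether. The rate is Σw·P(reduction ≥ t) in the self-selected arm and P(reduction ≥ m) in the assigned arm.

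| Shares | Reduction (μ, σ) | Self-selected | Assigned | Difference (points) |
|---|---|---|---|---|
| equal thirds | 0, 20 | 17.8% | 15.9% | +1.9 |
| equal thirds | 20, 20 | 50.0% | 50.0% | 0 |
| equal thirds | 15, 10 | 35.6% | 30.9% | +4.7 |
| equal thirds | 25, 10 | 64.4% | 69.1% | −4.7 |
| 50-0-50 | 15, 10 | 37.9% | 30.9% | +7.0 |
| 50-0-50 | 25, 10 | 62.1% | 69.1% | −7.0 |

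Example, third row: (0.691 + 0.309 + 0.067)/3 = 0.356 against 0.309. Nobody's behaviour differs between arms, yet the outcome does, and the sign depends on whether the typical reduction lies below or above the mean target.

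**Step 3: screen time with no effect of choosing.** Assume reduction = min(target, capacity), capacity N(20, SD 8, 10 or 15), equal thirds against a constant 20. Targets are either unrelated to capacity (spread only) or ordered by capacity (spread plus fit). At capacity SD 10 the mean reductions are 16.0 (constant, SD 5.8), 14.8 (unrelated, SD 7.5) and 18.3 (ordered, SD 9.0). For the ordered case d = (18.29 − 16.02)/√((8.96² + 5.83²)/2) = 2.27/7.56 = 0.30. Other variation in screen time of SD e adds e² under the root; at e = 20, d = 2.27/√(57.1 + 400) = 0.11.

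| Other variation, e (points) | Unrelated v constant, d | Ordered v constant, d |
|---|---|---|
| 0 | −0.26 to −0.09 | +0.26 to +0.30 |
| 10 | −0.13 to −0.06 | +0.14 to +0.21 |
| 20 | −0.07 to −0.04 | +0.08 to +0.14 |
| 30 | −0.05 to −0.03 | +0.05 to +0.10 |

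A second response rule (meet a target up to 5 points above capacity, otherwise give up; e = 10 to 30) gives +0.18 to +0.38 when people choose by capacity and −0.23 to −0.09 when the same targets are shuffled at random. Sign and size therefore depend on the response rule, the choice pattern and the residual variation, none of which the document states.

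**Step 4: percent versus minutes.** Take baselines of 240, 400 and 560 minutes. If the 30/20/10% targets are chosen in that order, the mean target is (72 + 80 + 56)/3 = 69.3 minutes; in the reverse order it is (24 + 80 + 168)/3 = 90.7. A common 20% gives 80.0. Equal mean percentages need not mean equal mean minutes.

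**The case against.** The best defence has four parts.

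- **The sentence is qualified by the words on average.** Read narrowly, it says that mean targets match, which is true of percentages. But the preceding sentence already says that; the further claim that nothing else differs is what fails.
- **Fit is part of choosing.** This largely stands. People who choose will tend to pick a target that suits them, and in a pragmatic trial that belongs to the intervention. It supports a package reading and does not support isolating the act of choosing. Marginal spread is not inherent in choice in the same way.
- **The Discussion discloses the misfit.** It does, and so the authors describe a package there. The Intervention-2 sentence remains at odds with it.
- **The second objective names no mechanism.** Correct. It asks only about the efficacy of self-selected versus assigned targets; cognitive dissonance appears only in the Discussion, as an additional reason. A reader might infer that the objective itself credits motivation or commitment, but the text does not say so.

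A reader might also infer that spread and fit produce a spurious effect as large as the planned d = 0.12. The document does not support that. It does not say which SD its d uses, and the larger values in Step 3 leave out all other variation in screen time. With 20 points of it, the ordered case gives +0.08 to +0.14 and the unrelated case stays below 0.12 in size. An effect that large is possible but not shown.

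**Conclusion.** The concern holds in a limited form. The claim that the two incentive arms differ only in choice versus assignment is not a property of this design: target spread (SD about 6 to 10 points against 0, under assumed shares) and person-target fit differ as well. This would disappear for spread only if all self-selected participants picked the same option, which the protocol does not expect.

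A reader might go further and call the comparison biased or invalid. It is neither. Randomisation protects it as a comparison of two packages. What cannot be drawn from it is the effect of choosing by itself. For target achievement rate, spread alone can shift the result by 0 to about 7 percentage points either way under the assumed reduction distributions. For screen time, neither the size nor the sign of the non-choice component can be obtained from the document. The weight is moderate: it changes what the second objective can conclude, not whether the comparison may be made.

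**What to change.** 1. Delete the sentence under Intervention-2 that makes choice the only difference, or qualify it to say that the mean percentage target is matched while spread and fit are not.
2. State the contrast of the second objective as own choice from a 10/20/30% menu versus one uniform target equal to the mean of those choices, and limit the conclusion to that package.
3. Report the distribution of targets by arm, in percent and in minutes, and read target achievement rate in that light. Results by chosen target should be descriptive only, because that grouping is not randomised.

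The cost is wording and one descriptive table from data already collected, together with a narrower conclusion.

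Giving the assigned arm the chosen targets in shuffled order is not recommended. The targets have been issued: 156 participants were randomised and three intervention weeks were complete at the original submission. Shuffling also equalises spread but not fit. In the model of Step 3 without other variation, the ordered case against a shuffled arm gives d = +0.43, +0.42 and +0.36 (capacity SD 8, 10, 15), compared with +0.26, +0.30 and +0.29 against the constant target. The difference that is not due to choosing would grow.
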